## Provisions for post-trial care {30}

Study personnel will try to reduce, control and treat any harm from trial participation. Immediate medical treatment will be provided at Lagos Mainland Hospital Yaba. As needed, referrals to appropriate healthcare facilities will be provided to the subject. The site study physician will then determine if an injury occurred as a direct result of the tests or treatments that are done for this trial.

If it is determined by the site study physician that an injury occurred to a subject as a direct result of the tests or treatments that are done for this trial, then referrals to appropriate healthcare facilities will be provided to the subject. In case of SAEs or other research-related injuries, the full cost of treatment and ensuing cost associated with any associated complications will be borne by study sponsors.

## Outcomes {12}

COVID-19 is a new disease and our understanding of it is evolving. To align this study with other international studies, the objectives, endpoints and some other aspects of the WHO’s Master Protocol [42] have been adopted as appropriate with modifications to suite the Lagos context. There are three objectives—one primary and two secondary objectives. Each objective has three sub-objectives—one for comparing chloroquine phosphate added on to standard therapy and standard therapy alone; one for comparing hydroxychloroquine sulphate added on to standard therapy and standard therapy alone; and one for comparing lopinavir/ritonavir added on to standard therapy and standard therapy alone.

A special WHO committee developed the ordinal scale that will be used in this study for the primary endpoint [43]. This study uses a combined endpoint (based on the WHO 7-point ordinal scale) of both “clinical status and mortality” at day 15. Hence, superiority can be demonstrated when either arm shows a significant effect on the variables for clinical status OR mortality by day 15. This endpoint is particularly useful in our population given the low mortality rate, and a combined endpoint would increase the study power. The secondary endpoints will enable evaluation of the effect of the trial medications on the rate of change in the clinical condition of COVID-19 patients, as well as the safety of the trial medications (Table 3).

**Table 3 Tab3:** LACTT objectives and endpoints

**Primary objectives**	**Primary endpoints**
1. To evaluate the clinical efficacy of chloroquine phosphate, hydroxychloroquine sulphate and lopinavir/ritonavir added on to standard therapy relative to standard therapy alone for treatment of individuals with laboratory-confirmed COVID-19 1.1 To evaluate the clinical efficacy of chloroquine phosphate added on to standard therapy relative to standard therapy alone for treatment of individuals with laboratory-confirmed COVID-19 1.2 To evaluate the clinical efficacy of hydroxychloroquine sulphate added on to standard therapy relative to standard therapy alone for treatment of individuals with laboratory-confirmed COVID-19 1.3 To evaluate the clinical efficacy of lopinavir/ritonavir added on to standard therapy relative to standard therapy alone for treatment of individuals with laboratory-confirmed COVID-19	*Seven-point ordinal scale assessed on day 15* 1. Not hospitalized, no limitations on activities 2. Not hospitalized, limitation on activities 3. Hospitalized, not requiring supplemental oxygen 4. Hospitalized, requiring supplemental oxygen 5. Hospitalized, on non-invasive ventilation or high flow oxygen devices 6. Hospitalized, on invasive mechanical ventilation 7. Death
**Secondary objectives**	**Secondary endpoints**
1. To evaluate the effect of chloroquine phosphate, hydroxychloroquine sulphate and lopinavir/ritonavir added on to standard therapy compared to standard therapy on the rate of progression/resolution of COVID-19 1.1 To evaluate the effect of chloroquine phosphate added on to standard therapy compared to standard therapy on the rate of progression/resolution of COVID-19 1.2 To evaluate the effect of hydroxychloroquine sulphate added on to standard therapy compared to standard therapy on the rate of progression/resolution of COVID-19 1.3 To evaluate the effect of lopinavir/ritonavir added on to standard therapy compared to standard therapy on the rate of progression/resolution of COVID-19	1. Clinical status on the 7-point ordinal scale on days 3, 5, 8, 11 and 29 2. National Early Warning Score assessed daily while hospitalized and on day 15 3. Duration of supplemental oxygen 4. Duration of mechanical ventilation 5. Duration of hospitalization or isolation 6. SARS-CoV-2 clearance time based on samples taken on days 3, 5, 8, 11, 15 and 29
2. To evaluate the safety of chloroquine phosphate, hydroxychloroquine sulphate and lopinavir/ritonavir added on to standard therapy compared to standard therapy in the treatment of individuals with laboratory-confirmed COVID-19 2.1 To evaluate the safety of chloroquine phosphate added on to standard therapy compared to standard therapy in the treatment of individuals with laboratory-confirmed COVID-19 2.2 To evaluate the safety of hydroxychloroquine sulphate added on to standard therapy compared to standard therapy in the treatment of individuals with laboratory-confirmed COVID-19 2.3 To evaluate the safety of lopinavir/ritonavir added on to standard therapy compared to standard therapy in the treatment of individuals with laboratory-confirmed COVID-19	1. Cumulative incidence of severe adverse events up to and including day 29 2. Changes in laboratory safety indices assessed on days 1, 8 and 15—haemoglobin concentration, platelet count, white blood cell count, glucose, creatinine, total bilirubin, ALT and AST

## Efficacy assessments

The schedule of assessments (SOA) in Table 4 outlines the baseline and follow-up assessments that will be done.

**Table 4 Tab4:** Schedule of assessments

Study period	Screening	Baseline	Follow-up days											
Day ± window	−1 or 1	1	2	3	4	5	6	7	8	9	10	11–14	15 ± 2	29 ± 3
1. Eligibility														
Informed consent	X													
Demographics and medical history	X													
Lung auscultation	X													
Chest radiography	X													
Confirm SARS-CoV-2 results^1^	X													
2. Study interventions														
Randomization		X												
Administration of study drugs^2^		X	X	X	X	X	X	X	X	X	X	X		
3. Study procedures														
Vital signs		X	X	X	X	X	X	X	X	X	X	X	X	
Clinical assessment^3^		X	X	X	X	X	X	X	X	X	X	X	X	
Review treatment/management		X	X	X	X	X	X	X	X	X	X	X	X	X
ECG for safety		X		X		X			X			X	X	X
Adverse event evaluation		X	X	X	X	X	X	X	X	X	X	X	X	X
4. Laboratory tests for safety														
Full blood count, liver function tests, creatinine^4^		X							X				X	
Pregnancy test for women of reproductive age	X													
5. SARS-CoV-2 testing														
PCR for SARS-CoV-2		X		X		X			X			X	X	X
6. Sample for future testing														
Oropharyngeal swabs^5^		X							X				X	
Blood/serum^5^		X							X				X	

^1^Time frame for test results: Results of tests done within 72 h of enrolment will be used

^2^Treatment duration: If the patient is still on admission after day 14, standard treatment will continue in all arms of the study while study medications stop on day 7 for chloroquine and hydroxychloroquine and on day 14 for lopinavir/ritonavir

^3^Clinical data to be collected: See the “Efficacy assessments” section for details

^4^Laboratory tests for safety: Blood—haemoglobin, white cell count, platelets, glucose, creatinine, bilirubin, alanine aminotransferase, aspartate aminotransferase

^5^Samples for future research: To be used when additional SARS-CoV-2 tests become available

### Measures of clinical status

On each study day while hospitalized or in isolation, the following measure of clinical status will be assessed:
SymptomsVital signsOxygen requirementNon-invasive mechanical ventilation (via mask)Mechanical ventilator requirement (via an endotracheal tube or tracheostomy tube)

### Ordinal scale

The ordinal scale is an assessment of the clinical status at the first assessment of a given study day. Each day, the worse score for the previous day will be recorded, i.e. on day 3, the day 2 score is obtained and recorded as day 2. The scale is as follows:
Not hospitalized, no limitations on activitiesNot hospitalized, limitation on activitiesHospitalized, not requiring supplemental oxygenHospitalized, requiring supplemental oxygenHospitalized, on non-invasive ventilation or high flow oxygen devicesHospitalized, on invasive mechanical ventilationDeath

### NEW score

The NEW score is based on 7 clinical parameters (see Table 5) and is being used as an efficacy measure. This will be evaluated at the first assessment of a given study day. These parameters can be obtained from the hospital chart using the last measurement prior to the time of assessment. This is recorded for the day obtained, i.e. on day 4, the day 3 score is obtained and recorded as day 3.

**Table 5 Tab5:** NEW score

Physiologic parameters	Score						
	3	2	1	0	1	2	3
Respiratory rate	≤8		9–11	12–20		21–24	≥25
Oxygen saturation	≤91	92–93	94–95	≥96			
Supplemental oxygen		Yes		No			
Temperature	≤35.0		35.1–36.0	36.1–38.0	38.1–39.0	≥39.1	
Systolic BP	≤90	91–100	101–110	111–219			≥220
Heart rate	≤40		41–50	51–90	91–110	111–130	≥131
Level of consciousness*				A			VPU

*Level of consciousness: alert (A), arousable only to voice (V) or pain (P), and unresponsive (U)

### Further assessments

Oropharyngeal swabs and blood/serum samples will be collected on days 1, 8 and 15 (while hospitalized or in isolation) and stored. Tests for viral shedding and antiviral antibodies are being developed and will be used to test the stored sample when they become available.

## Safety assessments

Study procedures are specified in the SOA. A study physician will be responsible for all trial-related medical decisions.
Physical examination
◦ A symptom-directed (targeted) physical examination will be performed to evaluate for any possible adverse event.Clinical laboratory evaluations
◦ Fasting is not required before collection of laboratory samples.◦ Blood will be collected at the time points indicated in the SOA. Clinical laboratory parameters include WBC, Hb, PLT, Cr, glucose, total bilirubin, AST and ALT.

If a physiologic parameter, e.g. vital signs, or laboratory value is outside of the protocol-specified range (Table 6), then the measurement may be repeated once if, in the judgment of the investigator, the abnormality is the result of an acute, short-term, rapidly reversible condition or was an error. A physiologic parameter may also be repeated if there is a technical problem with the measurement caused by malfunctioning, or an inappropriate measuring device (i.e. inappropriate-sized BP cuff).

**Table 6 Tab6:** Normal reference ranges for vital signs and safety assessments

Parameter	Reference range
Temperature	36.1–37.2°C
Pulse rate	60–100 beats/min
Respiratory rate	12–16 cycles/min
Systolic blood pressure	90–130 mmHg
Diastolic blood pressure	70–90 mmHg
Haemoglobin	12–17.5 g/dl
White blood cell count	4.00–11.0 × 109/l
Platelet count	150,000–450,000/μl
Creatinine	0.5–1.1mg/dl
Random glucose	76–150mg/dl
Total bilirubin	0–1.0mg/dl
ALT	0–40u/l
AST	0–37i.u/l

## Participant timeline {13}

The participant timeline is shown in Fig. 1.

**Fig. 1 Fig1:**
[figure not shown]
Schematic diagram showing the timeline for key processes in LACTT

## Sample size {14}

The sample size of 200 per arm has been calculated assuming an odds ratio (*OR*) of 2, 85% power and a 2-tailed test at level *α* = 0.05 and allowing for approximately 10% of participants to be lost to follow-up. The odds ratio represents the odds of improvement in the ordinal scale for treatment relative to control.

## Recruitment {15}

It is anticipated that patients with COVID-19 will present to the participating hospitals which are designated COVID-19 treatment centres. Therefore, no other efforts to recruit potential subjects are needed.

## Assignment of interventions: allocation

### Sequence generation {16a}

Prior to study initiation, a randomization list will be generated (using the statistical programming language R, version 3.6.3 to enable random assignment to each of the trial arms at each of the study sites using an equal allocation ratio (for instance 1:1:1:1 for four arms)). If arms are added to or dropped from the trial, randomization will proceed with an equal probability of assignment to each of the remaining arms.

Randomization will be stratified by site and at each site by severity of illness at enrollment yielding two strata: (1) asymptomatic (no clinical symptoms or signs) and (2) symptomatic (presence of clinical symptoms and/ or signs). The R code used to generate the randomization lists will store the seed so that the generated lists are reproducible.

The randomization list will be generated using permuted block randomization with two block sizes, with the larger block size chosen so that it is not a multiple of the smaller block. Using permuted block randomization rather than simple randomization will avoid the possibility of long periods of time during which participants are not allocated to one or more arms of the study—a scenario which could introduce bias to the study due to time effects. Two block sizes would make it more difficult for clinicians (who will be unaware of the block sizes) to guess any part of the allocation sequence, thus, reducing the potential for the introduction of selection bias by well-meaning staff members at study sites.

### Concealment mechanism {16b}

Eligible patients will be allocated to receive medication in individually numbered packs, according to the sequential order of the randomization list. These will be packaged by an unblinded team at the Lagos State central pharmacy lead by the clinical research pharmacist. These personnel are otherwise not involved in the management/care and assessment of the study participants. Neither the names of the investigational drugs nor the arm of the study will be included in the medication packs.

After assignment to interventions, trial participants, care providers and outcome assessors will remain blinded through the use of placebo that will have the same physical formulation, route of administration and dosing schedule.

### Implementation {16c}

The allocation sequence will be generated by a member of the trial team who will be based away from the trial sites and will not be involved in care of the participants, outcome assessment or management/analysis of unblinded data.

Clinical research assistants will enrol participants and assign intervention medication packs in sequential order of the randomization list and stratification.

## Assignment of interventions: blinding

### Who will be blinded {17a}

Trial participants, the clinical care team, research team, outcome assessors, data management personnel and data analysts will be blinded.

### Procedure for unblinding if needed {17b}

Individual envelopes containing the arm of the study and trial drugs enclosed in each numbered medication pack will be prepared for emergency unmasking in cases of serious adverse events (SAEs) and serious and unexpected suspected adverse reactions (SUSARs).

To unblind a participant, the study physician at the concerned study site will send the completed unblinding request form via email or manually to the clinical oversight lead at the study site. The study site pharmacist will be notified in the communication as well. The clinical oversight lead will notify the principal investigator and authorize unblinding.

Once the authorization request is approved, the site pharmacist will proceed to release the coded envelope for the research participant concerned. The site pharmacist will also file a copy of the unblinding request form in the pharmacy records for the study. The site pharmacist will ensure that the treatment assignment of the research participant concerned is shared with the study physician for the study site alone who would in turn take the necessary actions for the management of the patient and reporting adverse events and SUSARs.

## Data collection and management

### Plans for assessment and collection of outcomes {18a}

Participant data will be collected using case reporting forms (on mobile tablets with REDCap®) to be completed by trained clinical research assistants at baseline all through day 15 and then day 29. The use of REDCap® with periodic data reviews by a data management and auditing team will help the research team maintain data quality.

The schedule of assessments is shown in Table 4 and illustrated in Fig. 1. See Supplements for case reporting forms.

#### SOC available in each participating study site

Data on the standard of care available and provided to each participant will be summarized for each study site and the entire study population.

### Plans to promote participant retention and complete follow-up {18b}

Research participants in the treatment and control arms will be encouraged by the research team and given access to COVID-19 educational resources during the study. In addition, participants will receive communication from the research welfare team to attend to any concerns or questions participants may have during the study.

For participants who deviate or discontinue from the protocol, all outcome data relevant to the study prior to deviation or discontinuation from the study protocol will be collected.

### Data management {19}

The site investigator is responsible for assuring that the data collected is complete, accurate and recorded in a timely manner. Study data will be entered into REDCap® using tablets. Source documentation (the point of initial recording of information) will be signed and dated by the person recording and/or reviewing the data and will support the data transferred to REDCap®. The data entered into REDCap® will be compared with source documentation on a regular periodic bases as part of data quality assurance.

Due to the biohazard of SARS-COV-2 virus contamination, any original written source documents created at the bedside (i.e. in the ‘red zone’) will be treated as potentially infectious unless an effective means of decontamination can be instituted. Where possible, photographs, digital scans or other electronic data capture methods may be obtained instead of transporting the original written source documents from the ‘red zone’. Interview of subjects will be used for obtaining medical history.

### Confidentiality {27}

All records will be kept confidential to the extent provided by Lagos State University Teaching Hospital Health Research Ethics Committee (LASUTH HREC) regulations. The study monitors and other authorized representatives of the Sponsor may inspect all documents and records required to be maintained by the investigator, including but not limited to, medical records. Records will be kept locked and all computer entry will be done with coded numbers only. Clinical information will not be released without written permission of the subject, except as necessary for monitoring by LASUTH HREC.

### Plans for collection, laboratory evaluation and storage of biological specimens for genetic or molecular analysis in this trial/future use {33}

Any use of the sample or data for secondary research purposes, however, will be presented in a separate protocol and require separate HREC approval. Each sample will be labelled only with participant ID to protect subject confidentiality.

Each participant can withdraw consent at any time by notifying the study physicians or nurses in writing. If the subject subsequently changes his/her decision, the samples will be destroyed if the samples have not been used for research or released for a specific research project.

## Statistical methods

### Statistical methods for primary and secondary outcomes {20a}

The statistical methods are based mainly on the WHO Master Protocol [42], as outlined below.

#### Statistical methods for analyzing the primary outcome

The primary hypothesis is that the clinical status measured by a 7-point ordinal scale for each of the investigational arms (1, 2, 3) will be different from that of the placebo arm.

Boschloo’s test will be used to evaluate this primary hypothesis in all randomized participants (intention-to-treat analysis). For each comparison of a given arm to control, only participants concurrently randomized to those two arms will be included. Statistical significance will be claimed if the two-sided *P*-value is less than the monitoring boundary allocating a total type I error rate of 0.05 across interim analyses. The Boschloo’s test is being used instead of Fisher’s exact test because the interim results, as well as results within subgroups, will have small sample sizes based on the multiple primary outcomes within the subgroups.

The ordinal scale will be used to estimate a proportional odds model. The primary hypothesis test will be based on a test of whether the common odds ratio for treatment is equal to one. Nonetheless, estimation and confidence intervals do require the model to be correct. Accordingly, we will evaluate model fit using a goodness-of-fit likelihood ratio test. A stratified hypothesis test to account for baseline severity of disease will be used.

The distribution of severity results will be summarized by treatment arm as percentages, and participants without final outcome data will be excluded from the analysis.

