## Methods: participants, interventions and outcomes

### Study setting {9}

This trial will take place at health facilities designated for COVID-19 patients in Lagos State, Nigeria. The LACTT trial will be conducted at three of the health facilities designated for COVID-19 patients in Lagos State, Nigeria. The centres are Lagos Mainland Infectious Disease Hospital, Yaba; the Eti-Osa COVID-19 Isolation and Treatment Centre; and the Onikan COVID-19 Isolation and Treatment Centre Lagos State. The three centres manage patients domiciled in Lagos State, based on a similar state-wide protocol which aligns with the Nigeria Centre for Disease Control guideline for testing and management of COVID-19 disease. The proposed sample size distribution across the three centres is 200 participants per centre.

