#### Statistical methods for analyzing secondary outcomes

The following analyses will be performed for the comparison of each experimental arm to the placebo arm when full enrolment has been achieved. For these analyses, the alpha level used is that of the analysis for the primary outcome when full enrolment has been achieved.
The Mantel-Haenszel odds ratio estimator and test statistic will be applied to the strata defined by clinical signs and symptoms (asymptomatic versus symptomatic).Differences in time-to-event endpoints (e.g. time to negative SARS-CoV-2 status) by treatment will be summarized with Kaplan-Meier curves and 95% confidence bounds.Change in ordinal scale at specific time points will be summarized by proportions (e.g. proportion who have a 1-, 2-, 3- or 4-point improvement or worsening).Duration of event (e.g. duration of mechanical ventilation) will be summarized according to median days with quartiles.Incidence data (e.g. incidence of new oxygen use) will be summarized as a percent with 95% confidence intervals.Categorical data (e.g. 28-day mortality or ordinal scale by day) will be summarized according to proportions with confidence intervals on the difference or odds ratios for a binary or multiple category scale, respectively.Logistic regression analyses will be undertaken to assess the effect of covariates on outcomes.

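### Randomisation is stratified by site and symptom status, but the stated analysis strata leave out site; the effect is conservative, usually small, and easily avoided

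*Protocol article*

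**What the plan says.** All references are to the protocol article.

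- **Sequence generation {16a}:** "Randomization will be stratified by site and at each site by severity of illness at enrollment yielding two strata", namely asymptomatic and symptomatic.
- **Study setting {9}:** "The LACTT trial will be conducted at three of the health facilities designated for COVID-19 patients in Lagos State, Nigeria". The allocation therefore has 3 × 2 = 6 strata. The same section says the centres manage patients "based on a similar state-wide protocol".
- **Statistical methods for analyzing the primary outcome:** "The primary hypothesis test will be based on a test of whether the common odds ratio for treatment is equal to one", from a proportional-odds model, and "A stratified hypothesis test to account for baseline severity of disease will be used". Site is not named. The same section also says that Boschloo's test "will be used to evaluate this primary hypothesis in all randomized participants (intention-to-treat analysis", with no strata given.
- **Statistical methods for analyzing secondary outcomes:** the Mantel-Haenszel estimator and test are "applied to the strata defined by clinical signs and symptoms (asymptomatic versus symptomatic". A logistic regression on covariates is also planned, but the covariates are not listed.

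**The concern.** Permuted blocks within site force the arms to be balanced by site. If outcomes differ between centres, that balance removes between-site variation from the treatment comparison. A model without site does not know this: it leaves the variation in the residual, reports a standard error that is too large, and rejects a true null less often than 5%. An ordinal model also pulls the treatment odds ratio towards one when a prognostic factor is left out. Both effects lower power.

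Some difference between centres is conceivable. The comparator is whatever standard of care each site provides. The boundary between categories 2 and 3 of the primary scale is being in hospital or not, and the section on time to successful discharge concedes that discharge decisions are not always objective. What is at stake is efficiency against a planned power of 85%, not the validity of a positive result.

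**Working it through.** **1. The plan's own figure.** Sample size {14} gives 200 per arm for an odds ratio of 2, 85% power, two-sided 0.05 and about 10% loss, which leaves 180 evaluable. Whitehead's formula for the proportional-odds model is

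n per arm = 6(z₀.₉₇₅ + z₀.₈₅)² / [(ln 2)² · s], with s = 1 − Σp̄³

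Here 6 × (1.960 + 1.036)² / 0.4805 = 112.1, so n = 112.1/s. Reaching 180 needs s = 0.623. The article gives no category distribution, so 200 can be neither confirmed nor refuted. Assumed distributions with 45%, 60%, 62%, 70% and 80% of controls in category 1 give 151, 182, 188, 224 and 314 per arm after allowing for loss.

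**2. Simulation set-up.** One active arm against control, 180 evaluable each, with permuted blocks of 4 and 6 inside the six strata and 2,000 trials per setting. The model is

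logit P(Y ≤ k) = c_k + β·treatment + γ·symptomatic + δ_site

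with a Wald test of β = 0 at two-sided 0.05.

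From the documents: three sites, two symptom levels, equal allocation, odds ratio 2, 180 evaluable. Assumed: control distribution 0.62, 0.08, 0.20, 0.04, 0.02, 0.01, 0.03; 60% symptomatic; a symptom effect of 1.0 on the log-odds scale; equal-sized sites; the site effects below; no interim looks.

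Check: this distribution has s = 0.663, so the formula gives z = √(180 × 0.663 × 0.4805/6) − 1.960 = 1.131, a power of 87.1%. The simulated value with no site effect is 86.4%, within Monte Carlo error.

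**3. Effect of leaving out site.** The adjacent-site odds ratio is the step from one site to the next, so the outer sites differ by its square (2.25, 4 and 9).

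| Adjacent-site OR | Power: no strata | Power: symptom only | Power: symptom + site | Type I: symptom only | Type I: symptom + site | Model SE / true SD, site omitted (null) |
|---|---|---|---|---|---|---|
| 1 | 84.8% | 86.4% | 86.5% | 4.8% | 4.8% | 0.99 |
| 1.5 | 84.8% | 86.2% | 86.9% | 4.7% | 5.1% | 1.01 |
| 2 | 81.4% | 83.2% | 85.3% | 4.3% | 5.3% | 1.02 |
| 3 | 77.6% | 79.1% | 84.3% | 3.9% | 5.4% | 1.09 |

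Monte Carlo error is about 0.8 points on power, 0.5 points on type I error, and 1/√(2 × 2,000) = 1.6% on the SE ratio. The gains from adding site are 0.1, 0.7, 2.1 and 5.2 points. Only the last row shows a standard error clearly too large. The no-strata column is an unstratified proportional-odds test, not Boschloo's test; it shows only that dropping both factors loses more than dropping site.

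**4. Baseline status, kept separate.** With an adjacent-site odds ratio of 1.5 and a baseline score worth an odds ratio of 3 per point, power is 80.4% (symptom), 81.0% (+ site) and 84.9% (+ baseline). With 2 and 5 respectively, it is 74.0%, 75.5% and 84.3%. So baseline adds about 4 to 9 points and site 0.6 to 1.5. Type I error stays near 5% without and with baseline (4.9% and 4.7%; 5.1% and 5.3%).

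**The case against.** **Detail left to an analysis plan.** The primary section never says that severity is the only stratifier, and a condensed article may leave model terms to a document not shown. This has some force for the primary test. It has little for Mantel-Haenszel, whose strata are spelled out as the two symptom levels. In both places the article has chosen strata, and they are not those of the randomisation.

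**The centres may hardly differ.** They follow a similar state-wide protocol, and the remark about discharge concerns objectivity, not differences between centres. This stands: large site effects are an assumption, and at an adjacent-site odds ratio of 1.5 the gain is within simulation error.

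**The direction is safe.** This also stands. No false-positive risk arises. Part of the shrinkage in the odds ratio is non-collapsibility: mean log odds ratio 0.661 without site and 0.704 with it, at an adjacent-site odds ratio of 2. The sample-size section does not say whether its odds ratio of 2 is conditional on any factor.

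**A stronger reading.** A reader might infer that ignoring the baseline score also gives wrong error bars, because the symptomatic stratum pools mild to severe disease. The documents do not support that: the score is not a randomisation factor, so leaving it out can cost power but does not invalidate the test. Nor should a combined gain from site and baseline status be read as the cost of the stratification mismatch; most of it comes from an assumed baseline effect.

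**Conclusion.** The mismatch is real and stands in the text: six randomisation strata, but analysis strata that name only severity or symptom status. Its consequence is a conservative test. On assumed site effects, the standard error is about 0 to 2% too large and the power loss about 0 to 2 points for adjacent-site odds ratios up to 2; at 3, an extreme case, they are about 9% and 5 points. Including site costs nothing measurable if centres are alike (86.4% against 86.5%).

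These sizes rest on 180 evaluable per arm, the assumed outcome distribution and a single final analysis. Early looks were not simulated; at 25% information there would be about 45 per arm.

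The primary section leaves a further ambiguity: if the unstratified Boschloo's test is the primary one, both randomisation factors are ignored, and adding terms to the proportional-odds model would not change that. This is a worthwhile correction, not a threat to validity.

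**What to change.** - **Primary outcome section:** state that the test of the common odds ratio comes from a proportional-odds model with treatment, site and symptom status. State that this, and not an unstratified Boschloo's test, is the primary test.
- **Secondary outcomes section:** apply Mantel-Haenszel over the six site-by-symptom strata. It is run at full enrolment, where equal strata would hold about 180/6 = 30 participants per arm.
- **Optional:** prespecify oxygen requirement or ordinal status, measured before randomisation and first dose, as a prognostic covariate for power only. Do not use the day-1 worse score. The Ordinal scale section records the worst status over the day, and Table 4 puts randomisation and first dosing on day 1, so that score may include post-dose status.

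The first two changes take a sentence or two in each section and use data already held. The optional covariate also needs the record to show that the value was taken before dosing. Settle all of it before any unblinded comparison, and check how the model behaves at the smallest interim sample.
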